### 3.4. Data Security and Management

All quantitative data will be entered into a secure, password-protected electronic database by trained data entry personnel, with range and consistency checks applied. Qualitative interviews are transcribed verbatim by trained transcriptionists, and transcripts are reviewed for accuracy against the audio recording. All participant identifiers are replaced with unique numeric codes; a codebook linking names to participant IDs is encrypted and stored separately from all data, accessible only to the principal investigator.

Paper questionnaires and journaling material are stored in restricted-access, locked filing cabinets at a research laboratory of Applied Leisure Sciences at the Department of Physical Education and Sport Science, University of Thessaly. Only the principal investigator and authorized research assistants have access. All data will be retained for five years following study completion; paper documents are shredded, and digital/audio data are securely deleted thereafter, in accordance with institutional data retention policies and GDPR regulations.

### 3.5. Intervention Facilitator Qualifications and Training

Intervention sessions are delivered by certified modern dance educators meeting the following minimum qualifications: (1) bachelor’s degree or equivalent certification in dance or somatic movement; (2) minimum two years prior teaching experience with recreational adult populations; (3) formal training in mindfulness-based practices (MBSR certification, 200 h yoga teacher training, or safety-aware somatic training). Trauma-informed training is optional for facilitators with relevant background but not required, as the protocol maintains clear pedagogical boundaries; and (4) current CPR/First Aid certification. Prior to participant contact, each facilitator completes a 12 h standardized training module based on the Intervention Protocol Manual (Supplementary S1 [27]) and participates in 1–2 mock teaching sessions observed by the principal investigator, with written feedback incorporated before first participant session delivery.

Prior to each session, facilitators complete environmental standardization checklists documenting: studio temperature (17–22 °C), illumination (300–500 lux, LED flicker-free), acoustic baseline (≤50 dB), floor conditions (sprung or semi-sprung surface), room dimensions and participant spacing (3.5–4.0 m^2^ per participant), and confirmation of clear emergency exit pathways and visible first aid kit location (detailed specifications in Supplementary File S2 [27]).

Session attendance is recorded by the facilitator at each weekly session. If a participant misses a session, the site coordinator contacts them within 48 h to understand reasons and reschedule a make-up session if feasible, preferably within the same phase. Participants missing more than two consecutive sessions receive additional follow-up contact to assess barriers and provide support (childcare resources, transportation assistance, schedule accommodation).

Facilitators complete standardized fidelity checklists immediately post-session documenting: completion of all eight components, actual duration of each component, deviations from protocol with justification, participant engagement level, and any adverse events or clinical concerns. Facilitators also maintain a reflective journal after each session documenting session flow, participant engagement, emotional atmosphere, personal reflections on facilitation quality, adaptations made, and any participant concerns. Reflection journals are reviewed weekly during supervision.

Facilitators meet with a designated supervisor (principal investigator or designated research staff) for weekly 1 h supervision sessions (or biweekly if multiple facilitators). Supervision includes fidelity review, problem-solving regarding participant responses or challenges, discussion of participant safety concerns, facilitator well-being and support needs, and any protocol adaptations with documented justification.

### 3.6. Mid-Intervention Qualitative Assessment (T1, Week 8)

At Week 8, qualitative data collection captures participants’ lived experience at the intervention midpoint, creating a comparative baseline for the post-intervention assessment. A purposive subsample of approximately 30 intervention participants is selected via maximum variation sampling (varying by age, gender, prior experience, and baseline distress). These participants complete a 20–30 min interview exploring six core phenomenological domains (embodied awareness, emotional regulation, nervous system activation, relational connection, meaning-making, and movement confidence). The interview guide (Supplementary File S3) [27] specifically probes shifts in embodied experience attributed to the first two phases (Foundations and Embodied Exploration), allowing for longitudinal tracking of the learning trajectory.

Cumulative weekly journals from Weeks 1 to 8 are collected to form the Phase 1 and Phase 2 dataset. Unlike retrospective interviews, these entries provide real-time, week-by-week accounts of the embodied learning process before the onset of the final Expressive Integration phase (full journaling prompts available in Supplementary File S3 [27]). Control group participants do not engage in interviews or journaling.

### 3.7. Post-Intervention Assessment (T2, Week 12)

At Week 12, all randomized participants complete the final assessment to evaluate intervention outcomes and longitudinal progression. Both intervention and control groups complete the identical battery of five outcome measures administered at baseline (T0), following standard administration procedures to ensure comparability. The same subsample of participants interviewed at T1 completes a second semi-structured interview (20–30 min). The T2 guide (Supplementary File S3) [27] retains the core phenomenological domains but pivots the inquiry toward integration and transformation. Participants reflect on their trajectory across the full 12-week period, enabling an analysis that compares T1 (midpoint) and T2 (endpoint) narratives to map the developmental arc from early somatic grounding to late-phase creative expression.

Intervention participants complete a final journal entry (Supplementary File S3) [27] specifically designed to export a retrospective comparison between their Week 1 and Week 12 embodied states. This completes the qualitative dataset, which is then stratified into three Phase-aligned segments (Weeks 1–4, 5–8, 9–12) for Reflexive Thematic Analysis (coding framework detailed in Supplementary File S3 [27]).

The qualitative strategy at T2 focuses on triangulation: phase-specific journal themes are cross-referenced with longitudinal interview narratives to construct a mechanistic explanation of embodied change. Control group participants complete only the quantitative assessment, preserving the distinction between outcome evaluation (quantitative/comparative) and process evaluation (qualitative/descriptive).

## 4. Expected Results

Based on the integrated theoretical framework (polyvagal theory, motor learning science, embodied phenomenology) and the structured 12–week protocol design, the following outcomes are expected:

Quantitative outcomes. Intervention participants are expected to demonstrate significantly greater improvements from baseline to post-intervention compared with controls on primary outcome measures: increased life satisfaction and subjective happiness, decreased psychological distress, and enhanced mindful attentional capacity and leisure involvement. These improvements are hypothesized to reflect the intervention’s integration of nervous system regulation (breath-movement synchronization), embodied awareness practices, and relational belonging within the dance context.

Qualitative outcomes. Phenomenological analysis of interview and journal data is expected to reveal a progressive developmental arc across the three intervention phases. Early-phase reflections are anticipated to center on foundational somatic awareness and nervous system regulation; mid-phase reflections to incorporate relational presence and emotional attunement; and late-phase reflections to synthesize embodied learning, relational connection, and authentic expression into coherent narratives of transformation. Control group reflections are expected to remain focused on conventional dance engagement (technique, enjoyment) without the developmental trajectory or transformational narratives anticipated in the intervention group. Individual variability in response will be examined descriptively to identify participant and contextual factors influencing intervention responsiveness.

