### 1.2. Aim and Objectives

The aim of this study is to develop and theoretically justify a comprehensive, 12-week integrated dance-mindfulness protocol grounded in polyvagal theory, motor learning science, and embodied phenomenology. The protocol systematically operationalizes the cultivation of nervous system resilience, technical dance competence, authentic creative expression, and social belonging within structured modern dance theater (Imperial Society of Teachers of Dancing-ISTD syllabus [26]) for community-based adult dancers. The study investigates whether this integrated protocol produces measurable psychological improvements compared to standard dance instruction, and whether participants report enhanced embodied meaning-making and somatic awareness through phenomenological accounts. The specific objectives are:(1)To develop and operationalize a comprehensive, 12-week integrated dance-mindfulness protocol grounded in neuroscience, motor learning, and embodied phenomenology that systematically integrates theory with practice.(2)To evaluate the protocol’s effectiveness using a mixed-methods RCT design comparing intervention and control groups on quantitative and qualitative outcomes.(3)To evaluate the intervention’s effectiveness on psychological well-being and embodied experience.

Based on the theoretical framework and structure of the 12-week intervention, it is hypothesized that participants in the dance mindfulness intervention group will demonstrate significantly greater improvements than those in the control group across primary quantitative outcomes (life satisfaction, subjective happiness, psychological distress, mindful attentional capacity, and leisure involvement) and secondary qualitative outcomes (enhanced somatic awareness, nervous system resilience, technical confidence, creative expression, relational belonging, social connection and embodied meaning-making).

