Weekly Journaling Prompts. Participants provide weekly written reflections using standardized prompts distributed at the end of each session (5–10 min per entry). Prompts guide attention to: (1) breath and embodiment (e.g., “Which movements or exercises helped you feel embodied or aware of your internal sensations?”); (2) emotional states and internal reactions (e.g., “Did you notice any shifts in mood, tension, or energy throughout the session?”); (3) awareness of movement and creative exploration (e.g., “Were there moments where movement felt effortless, challenging, playful, or meaningful?”); (4) meaning-making (e.g., “How did today’s experience connect with your life outside the studio?”); and (5) change across sessions (e.g., “Compared to earlier weeks, do you notice any changes in your awareness, emotions, or movement?”). Journals are completed on standardized paper forms, collected weekly, and analyzed for thematic patterns regarding embodied experience, affective change, and perceived transformation.

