## 6. Conclusions

This protocol outlines a comprehensive, evidence-informed 12-week integrated dance-mindfulness intervention designed to systematically operationalize polyvagal theory, motor learning science, somatic education, and embodied phenomenology into coherent pedagogical practice. Grounded in principles of progressive nervous system development, technical skill optimization, and relational attunement, the proposed three-phase framework addresses a critical gap in recreational dance education by bridging abstract neuroscientific theory and concrete teaching methodology. The intervention responds to what recreational dancers authentically seek: nervous system resilience, embodied confidence, authentic creative expression, and social belonging—motivations that are largely absent from both clinical and elite professional dance research.

If supported by future data, this approach may offer a replicable and adaptable model for transforming recreational dance from technical skill development alone toward a comprehensive well-being practice grounded in contemporary neuroscience and embodied meaning-making. Beyond recreational dance, findings will inform contemplative movement education broadly (yoga, tai-chi, Pilates, qigong) and clarify scalability across educational, community, and clinical settings, with implications for integrating neuroscience-informed embodied practice into diverse organizational contexts. This protocol contributes to evidence-based pedagogical innovation by demonstrating that systematic integration of nervous system regulation, motor learning, somatic reflection, and relational engagement produces superior psychological and embodied outcomes compared to traditional dance instruction alone, fundamentally advancing how movement education serves adult psychological well-being and authentic self-expression.

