Journaling Content & Process	Phase 1 Structure (10–15 min total): Opening (1–2 min): “Find a comfortable place to sit. Take a pen and paper. We’ve moved together for 70 min. Now we invite your mind to articulate what your body has learned”. Prompts (8–10 min): Facilitator reads 2–3 of the following: (1) “What did your body discover today?”, (2) “Where did you feel most alive?”, (3) “What surprised you about yourself in movement?”, and (4) “What did you learn about your nervous system?” Participants write freely, not answering all prompts, just following what resonates. Closing (1–2 min): “Set your pen down. You’ve documented your individual learning journey. Your words are evidence of your transformation”.	Phase 2 Structure (12–17 min total): Opening (1–2 min): “Today we invite you to write about what you’ve learned about yourself and about connection. How is your body changing in relation to others? What are you discovering about connection, about belonging?”. Prompts (9–13 min): Facilitator reads 3–4 of the following: (1) “What did you feel moving alongside others today?”, (2) “Where did you experience connection? With your body? With others? With the space?”, (3) “What patterns are you noticing across these weeks of practice?”, (4) “What nervous system shift have you noticed in yourself? What evidence do you have?”, and (5) “What surprised you about your own presence or authenticity today?” Participants write to 2–3 prompts, following internal resonance. Facilitator model’s reflective stance: “There’s no right answer. Your authentic writing is your data”. Closing (1–2 min): “Your words are becoming evidence of your transformation from individual work to relational presence. That’s essential learning”.	Phase 3 Structure (14–20 min total): Opening (2–3 min): “We’re at the end of 12 weeks. Today we invite you to write about your complete transformation across four dimensions: your individual nervous system, your relational attunement, your inhabitation of space, your sense of belonging to community. How have you transformed across all four? Write your authentic truth”; Prompts (10–14 min): Facilitator reads 4–5 of the following (participants choose which to write to): (1) “Individual Dimension: How has your nervous system transformed? What evidence of regulation, authenticity, embodied presence do you notice?”, (2) “Relational Dimension: How has your capacity for connection shifted? What have you learned about moving with others? About feeling felt?”, (3) “Spatial Dimension: How do you inhabit space now? What’s different about your relationship to the room, to the ground, to your body’s presence in space?”, (4) “Social Belonging Dimension: What do you feel when you think of ‘we’, this community? How has belonging changed your sense of self?”, and (5) “Integration: What is the relationship between these four dimensions? How do they support one another?” Participants write continuously, following their own pace. Facilitator creates sacred silence: “I’m here. Your words matter. Take your time”. Closing (3–5 min): Comprehensive integration cue [57,58].

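### The hypothesis, expected results and conclusion compare qualitative outcomes with controls, but controls supply no qualitative data, and the predicted phase arc is confounded with phase-specific prompts

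*Protocol article*

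**What the plan says.** **The comparison.** Section 1.2 states in one sentence that intervention participants "will demonstrate significantly greater improvements than those in the control group across primary quantitative outcomes" (five are listed) "and secondary qualitative outcomes (enhanced somatic awareness, nervous system resilience, technical confidence, creative expression, relational belonging, social connection and embodied meaning-making"). The control comparison governs both lists. Section 4 predicts the content of control reflections: "Control group reflections are expected to remain focused on conventional dance engagement (technique, enjoyment) without the developmental trajectory or transformational narratives" anticipated for the intervention arm. Section 6 says the protocol contributes by showing that the integrated approach "produces superior psychological and embodied outcomes compared to traditional dance instruction alone".

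**The data.** Section 3.6 says "Control group participants do not engage in interviews or journaling". Section 2.6 withholds reflective prompts from controls, Section 2.7 confines qualitative data to the intervention group, and Sections 3.2 and 3.7 limit controls to the questionnaires. Section 3.7 separates a comparative quantitative strand from a descriptive qualitative one.

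**The arc and the prompts.** Section 4 also predicts a progression of themes across the three phases, from interviews and journals. Section 2.5 describes the journals thus: "Participants provide weekly written reflections using standardized prompts distributed at the end of each session (5–10 min per entry"), with five topics. Table 9 gives different prompts and longer durations in each phase. Its Phase 3 opening reads "Today we invite you to write about your complete transformation across four dimensions". Section 3.7 turns the T2 interview guide towards integration and transformation.

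**The concern.** A hypothesis of greater improvement than controls needs observations from controls. For the seven qualitative outcomes the design excludes them, so the hypothesis can be neither supported nor contradicted, whatever the intervention participants say. The risk is that intervention-only narratives are later reported as though they showed superiority over ordinary dance classes, in line with Sections 4 and 6.

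The second issue concerns the within-arm account. If the questions change with phase in the same direction as the predicted answers, a change in themes cannot be attributed cleanly to a change in participants. Section 3.7 nevertheless intends to build a mechanistic explanation from the phase-split journals and the two interviews.

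**Working it through.** No stated figure needs reproducing; the check sets the sections side by side.

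**Step 1. Who supplies what** (planned numbers from Section 2.4; sources from Sections 2.5, 2.7, 3.2, 3.6 and 3.7).

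| Source | Intervention (76) | Control (38) |
|---|---|---|
| Five questionnaires, T0 and T2 | yes | yes |
| Weekly journals | yes | 0 |
| Interviews, Weeks 8 and 12 | about 30 | 0 |
| Qualitative data before the first session | none | none |

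A between-group contrast needs data from both arms, and here one arm contributes 0 of 38. There is no pre-intervention qualitative baseline either: the first journal follows the Week 1 session and the first interview is at Week 8.

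**Step 2. Could the questionnaires stand in?** Table 1 covers life satisfaction, depression/anxiety/stress, mindful attention, happiness and leisure involvement. None is described as measuring somatic awareness, nervous system resilience or embodied meaning-making. Section 2.1 assigns these to the qualitative strand. The embodied part of the Section 6 claim therefore has no controlled data behind it.

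**Step 3. Predicted arc against Table 9 prompts.**

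| Phase | Section 4 predicts | Table 9 asks | Where the match is loose |
|---|---|---|---|
| 1 | Somatic awareness, regulation | What the body discovered; what was learned about the nervous system | Two of four prompts are open; the closing cue already speaks of transformation |
| 2 | Relational presence, emotional attunement | Moving with others; connection; belonging | One prompt still asks about a nervous system shift; no listed prompt names emotional attunement |
| 3 | Narratives of transformation | Transformation in four dimensions | Participants choose prompts; authenticity is also prompted in Phase 2 |

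The direction agrees in every phase, but the correspondence is not exact. The interviews are not a fully independent check: the T1 guide probes shifts attributed to the first two phases (Section 3.6), and the T2 guide pivots towards transformation (Section 3.7).

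**Step 4. Two descriptions of journaling.** Sections 2.5 and 3.2 give five topics in 5–10 min. Section 3.3 gives 10–20 min, and Table 9 gives 10–15, 12–17 and 14–20 min for Phases 1, 2 and 3. The ranges meet only at 10 min in Phase 1 and do not overlap in Phases 2 and 3. The article does not settle which prompts produce the analysed text.

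**The case against.** **Qualitative work needs no control group, and the operative sections already say so.** This stands. Section 2.7 plans no inferential test on qualitative data, and Section 3.7 calls the strand descriptive. No allocation, primary outcome or sample size depends on the disputed sentences. That keeps the repair to wording, but it does not rescue the hypothesis in Section 1.2 or the prediction in Section 4, which say the opposite.

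**The conclusion is conditional.** The paragraph in Section 6 opens by making the approach depend on future data, and the quoted sentence does not call embodied outcomes qualitative. It is the weakest of the three places. The sentence itself still carries no condition.

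**Supplementary File S3 is not shown.** It may settle the prompt wording. It cannot supply control data that the article explicitly rules out.

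**The prompts do not dictate the answers.** A reader might infer that the arc is scripted and would appear even if nobody changed. The documents do not support that. Participants choose among prompts and write freely. Phase 2 still asks about the nervous system, and the transformation cue runs from Phase 1 rather than arriving with the late phase. The interview guide in Section 2.5 asks openly what changes, if any, were noticed, and Section 3.2 uses interviewers not involved in delivery. What remains is confounding: prompted and genuine change cannot be told apart.

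**Conclusion.** The concern holds. The secondary hypothesis, as a comparison with controls, cannot be tested on any of its seven qualitative outcomes, because 0 of 38 planned controls provide the relevant data. This rests on explicit statements in the article, not on an omission that a supplement or analysis plan could fill. Treating the embodied claim in Section 6 as equally unsupported assumes that no Table 1 questionnaire is meant to measure embodied experience, as the article's own descriptions indicate.

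The prompt issue is a caution about interpretation. Phase-specific prompts and the T2 guide lean towards the predicted arc, so a change in themes across phases is not by itself evidence of developmental change or of mechanism. How far the prompts would produce the arc on their own is not known. The quantitative comparison on the five questionnaires is unaffected.

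**What to change.** 1. In Section 1.2, restate the secondary qualitative objective as a descriptive account within the intervention arm, matching Sections 2.7 and 3.7.
2. In Section 4, delete the prediction about control reflections.
3. In Section 6, limit the comparative claim to the five questionnaire outcomes and make it conditional on the results.
4. State that a change in themes across phases may have been prompted by the phase-specific journal prompts and the T2 guide, and do not present it as evidence of developmental change or mechanism.
5. Reconcile the prompt set and journaling duration in Sections 2.5 and 3.2 with Section 3.3 and Table 9, and say which text is analysed.

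These are text changes. The cost is a narrower claim.

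Basing the phase analysis on the Section 2.5 prompts instead would not be a clean repair. That section gives example questions only, does not say they are identical every week, includes a topic on change across sessions, and names no relational topic. Running it alongside Table 9 also adds time. The first seven components in Section 3.3 total 9+14+9+4+8+15+8 = 67 to 10+15+10+5+9+17+9 = 75 min. Journaling of 10–20 min brings this to 77–95 min, and a further 5–10 min gives 82–105 min against stated sessions of 90–100 min.

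Keeping the comparative hypothesis would require the same neutral qualitative data from both arms. That is a design change, and since journaling is an intervention component withheld from controls (Section 2.6), journals could not be added to the control arm without altering the contrast.
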